**Concomitant medications during the study phase**

The use of any drug (including medications of current use and not controlled) during the initial phase of diagnostic investigation and anti-TB therapy will be monitored and registered on the Concomitant Medication Form. The concomitant antimicrobials with known antituberculosis activity (for instance, rifabutin, rifapentin, amoxicilin/clavulanic acid, amicacin, canamicin, streptomycin, ofloxacin, ciprofloxacin, levofloxacin, sparfloxacin, gatifloxacin, gemifloxacin, linezolid, capreomycin, clofazimine, cycloserine, ethionamide, sodium para-aminosalicylate) will be registered for an analysis *a posteriori* of the final diagnosis. Every patient that receives more than 4 consecutive days of some of the above listed medicines will be classified as being in a regimen that may potentially alter the clinical evolution and his/her inclusion as a non-TB case. Antimicrobials with no anti-tuberculous activity known can be prescribed for intercurrent infections at the investigator’s criterion.

**3.8. Definition of a TB Suspect Case, Active TB Case and Discordance Analysis**

**Pulmonary and /or pleural pulmonary form**

Every patient under pulmonary TB suspicion that presents respiratory signs/symptoms and with alterations in the chest X-ray will be classified in three groups;

a) Typical pattern of TB: infiltrated in upper third (LS or apical seg of LI), with or without cavity; bilateral miliar infiltration; unilateral pleural hemorrhage with upper lobe infiltration .

b) Intermediate pattern of TB: infiltrated in middle or lower third, with or without cavity in these areas; isolated pleural hemorrhage, infiltrated in upper thirds of undetermined activity; diffuse abnormalities (not miliar); mediastinal or hilar enlargement .

c) Atypical Pattern of active TB: multifocal hypotransparency images; alveolar hypotransparency images; calcified nodules.

“**Confirmed TB case"** will be defined as the patient with at least one positive culture for *M. tuberculosis* in L-J or MGIT960*.*

**“Probable TB case"** will be defined as the patient that presents negative results to culture with one or more of the following characteristics:

a) clinical answer to the treatment (defined as improvement to X-ray, b) decrease of the cough and 3% weight gain in relation to the beginning of the treatment) and absence of alternative diagnosis;

Patient not classified as confirmed case or probable TB will be considered "non- TB."

**Treatment failure:** patient that remains with positive bacteriological test (two samples in a 30 day interval) after 5 months of treatment, standardized by MH

High risk factors for resistant TB:

a) Relapsing TB (previous complete treatment for TB with apparent cure), b) Treatment failure (patient under treatment ≥ 4 months with positive bacilloscopy), c) Patient’s contact with multidrug resistant-TB.

3.9 **Main outcome**  The primary outcome was defined as the proportion of patients in each group whose initial prescription changed by the second month after randomization. The ‘change’ could be initiating or stopping TB treatment.

**Secondary outcomes-**

-The secondary outcomes were the mean time to changing the initial clinical prescription,

-The proportion of patients with positive culture and positive smear microscopy for TB,

-The proportion of patients initiating treatment before test results,

-The occurrence of severe adverse events

-Patient satisfaction with the overall treatment- Number of deaths by any cause in the patients included in the study.

- Proportion of patients with TB diagnosis sensitive or resistant to anti-TB medicines (RIF, INH, SM and EMB), with the methods employed in the study.

- Proportion of patients that undergo anti-TB treatment failure during the therapy.

- Proportion of drug resistant TB development in the patients that used the different diagnostic methods and that were classified as treatment failures.

- Proportion of bacteriological conversion (bacilloscopy and culture for mycobacterium) due to the anti-TB treatment at the end of the second and sixth month of anti-TB treatment.

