**1) RATIONALE**

The rapid diagnosis of TB is important in order to prevent the disease. However, little progress has been done in the last 50 years. New techniques such as the amplification of nucleic acids and automated systems using culture in liquid medium are very expensive and depend on sophisticated techniques that make them inadequate for routine use in "low income countries." Yet, even in "middle income countries" as in Brazil, where such technologies could be used in the public system and TB is endemic, the TB diagnosis has been based only on clinical suspicion, chest radiography and bacilloscopy exam (BAAR) of the sputum. Despite the low sensitivity (40% to 60%) of the sputum bacilloscopy, it is still one of the most important tests for the TB diagnosis, as it detects the patients that present a higher chance of infecting the community. Besides, in the developing countries a low incidence of the non tuberculosis mycobacterium (NTM) disease is observed. In these areas, the sputum bacilloscopy has a highly positive predictive value. However, in most of these countries, in practice, the culture for mycobacteria, whose sensitivity is higher (80% to 85%) than the bacilloscopy in the diagnosis of the lung TB, is carried out in solid medium, Löewenstein-Jensen (LJ), and is only performed in selected clinical cases (cases of treatment failure, patients with negative bacilloscopy). The major problem of the LJ culture is its long time of incubation (4 to 6 weeks) and the sensitivity test is accomplished from the culture and not from the clinical specimen, which demands several additional weeks for the obtainment of the results. In practice, in these countries, with the universal use solely of the sputum bacilloscopy, about 30% to 40% of the patients assisted in Primary Health Units in developing countries such as Brazil are treated of TB without bacteriological confirmation.

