The development of new products for the tuberculosis diagnosis faces some challenges, the same way it is observed in the development of new medicines for neglected diseases: scarce financial resources and the market logic that reduces considerably the interests of large companies, since the use of the final product will be almost totally accomplished by the government of the different countries, usually not fulfilling their contracts, exactly where such diseases are prevalent.

In the last years, it has been emphasized the necessity of the accomplishment of Phase IV clinical trials, called pragmatic, which assess interventions in the nearest possible way to the real conditions in which they are applied in the clinical practice, serving as a support for taking decisions, in opposition to the so called explanatory Phase I, II, III clinical trials, carried out in more controlled conditions, answering questions about if and how does an intervention work; these questions are necessary to obtain the registration and commercialization of products.

Pragmatic studies, for being developed in routine conditions, do not complicate the usual practice and for this reason they are cheap and get the voluntary collaboration of the team.

The attainment of such studies does not raise great interest from the industries and unfortunately their execution usually is not considered a priority on the part of the governments be it at federal, state or municipal level or by the public policies formulators.

Studies already accomplished have shown that the BACTEC MGIT 960 performance is equalled to the BACTEC 460 one, with the advantage of being a non-radiometric method, supplying results in less time than the LJ solid medium. Recently, the Food and Drug Administration (FDA) has approved the automated method that uses the liquid medium called BACTEC MGIT (Mycobacteria Growth Indicator Tube) 960 that besides being as non-radiometric as the previous version (BACTEC460), provides a reliable TB and DST diagnostic result in less time than the LJ solid medium (10 to 15 days).

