**3.10. Size Sample**

Concerning the primary outcome, the smallest absolute difference considered important by a panel of specialists working at HUCFF was 10% presents the number of patients required to have an 80% chance of detecting this difference at the 5% level of statistical significance. We intended to recruit at least 770 participants.

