**3.11 -. Data analysis**

Socio-demographic and clinical characteristics between groups at trial entry will compared. For dichotomous outcomes, we will calculate the proportions for both groups, and for continuous outcomes, we will calculate the means, standard deviations and medians. We will used intention-to-treat analysis to calculate the relative risk, the risk difference, the number needed to treat and the 95% confidence intervals for these parameters. No subgroup analysis will be pre-specified. All analyses will be performed using SPSS software

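### The mean time to changing the prescription exists only for patients who change, so it compares groups selected after randomisation by the primary outcome

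*Protocol*

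**What the plan says.** The primary outcome (Protocol 3.9, and the same in the synopsis) is the "proportion of patients in each group whose initial prescription changed by the second month after randomization". It adds: "The ‘change’ could be initiating or stopping TB treatment". So a patient whose first decision is left standing does not have the event.

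The list of secondary outcomes opens with: "The secondary outcomes were the mean time to changing the initial clinical prescription". Section 3.11 gives one rule for such a quantity: "for continuous outcomes, we will calculate the means, standard deviations and medians". The same section names "intention-to-treat analysis to calculate the relative risk, the risk difference, the number needed to treat and the 95% confidence intervals", which are measures for dichotomous outcomes.

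The protocol gives no time value for patients who never change, and says nothing of death or loss for this outcome. It does not state the outcome's time window. In the table of outcomes, item 9 (time of schedule change) is taken from record cards at the end of months 2 and 6. Section 3.7 follows all patients for 8 weeks, and longer only those diagnosed with active TB.

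**The concern.** The protocol never writes 'among those who changed', but that is the only group for which a plain mean, standard deviation or median can be computed under these rules. Membership of the group is decided after randomisation, by the primary outcome. If MGIT alters who changes, the two groups of changers differ in composition, and the difference in means mixes speed with selection. A median among changers has the same defect.

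This matters because speed is a large part of the case for MGIT. The Rationale sets a result in 10 to 15 days against 4 to 6 weeks of incubation for LJ, and the synopsis describes accuracy as similar. If MGIT adds changes on culture results, these come later than changes made on smear or clinical grounds, and they raise the MGIT mean. The test then loses credit for patients whose treatment was changed only because of it.

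**Working it through.** **1. How many patients have no time to average.** Section 3.10 gives a 10-point difference, 80% power, a 5% level and 770 patients. It states no control proportion. Assuming a two-sided test, 1:1 allocation and 40% v 50%:

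n per arm = (1.960 + 0.842)² × (0.40×0.60 + 0.50×0.50) / 0.10² = 7.849 × 0.49 / 0.01 = 384.6, so 385 per arm and 770 in total.

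The stated figure is reproduced. At these rates 0.60 × 385 = 231 LJ patients and about 0.50 × 385 = 192 MGIT patients have no time to change. The pair 50% v 60% also gives 770, and leaves 50% and 40% without a time. The sample size is used here only to show the scale.

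**2. What the mean among changers leaves out.** Let p be the proportion changed by day 60 and m the mean time among changers. Counting non-changers as 60 days, the restricted mean over all randomised patients is

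R = 60 − p(60 − m).

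The gain with MGIT is then

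R(LJ) − R(MGIT) = p(LJ) × [m(LJ) − m(MGIT)] + [p(MGIT) − p(LJ)] × [60 − m(MGIT)].

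The planned comparison shows only the bracket m(LJ) − m(MGIT). The second term, the gain from extra changes, is lost. With equal p, the direction is right.

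**3. The protocol's times, equal shares.** Assume 30% change at day 7 on smear or clinical grounds and 10% on culture in each arm, at day 42 (LJ) and day 15 (MGIT).
- Mean among changers, LJ: (0.30×7 + 0.10×42)/0.40 = 15.75 days.
- Mean among changers, MGIT: (0.30×7 + 0.10×15)/0.40 = 9.0 days.
- Restricted mean gain: 0.40 × 6.75 = 2.7 days.

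The direction is right.

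**4. The protocol's times, unequal shares.** As step 3, but MGIT has 20% culture-driven changes.
- Mean among changers, LJ at day 28 to 42: 4.9/0.40 to 6.3/0.40 = 12.25 to 15.75 days.
- Mean among changers, MGIT at day 10 to 15: 4.1/0.50 to 5.1/0.50 = 8.2 to 10.2 days.

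No combination reverses. The size is off, though. At day 42 v day 15 the difference among changers is 5.55 days. The restricted mean gain is 0.40×5.55 + 0.10×49.8 = 2.22 + 4.98 = 7.2 days. More than two thirds of the gain (4.98 of 7.2) is in the term that the planned mean drops.

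**5. When the direction reverses.** Keep 30% at day 7 and MGIT 20% at day 15 (mean 10.2), and let the LJ culture-driven share be c.
- LJ at day 42: (2.1 + 42c)/(0.30 + c) < 10.2 gives 31.8c < 0.96, so c is below about 3.0%.
- LJ at day 28: 17.8c < 0.96, so c is below about 5.4%.

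Reversal therefore needs far fewer culture-driven changes under LJ than under MGIT.

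**6. A reversal with MGIT at day 15.** Assume 40% change at day 7 in both arms, LJ culture adds none by day 60, and MGIT adds 10% at day 15.
- Mean among changers, LJ: 7.0 days. MGIT: (0.40×7 + 0.10×15)/0.50 = 8.6 days.
- Restricted mean, LJ: 60 − 0.40×53 = 38.8 days. MGIT: 60 − (0.40×53 + 0.10×45) = 34.3 days.

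MGIT looks 1.6 days slower, yet no patient group changes later and the restricted mean is 4.5 days shorter. With a 56-day horizon (8 weeks) the gain is 0.10 × (56 − 15) = 4.1 days.

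**The case against.** **Reversal.** A reader might infer that the planned mean will show MGIT as slower. The documents do not support that. With similar accuracy and the stated laboratory times, the mean among changers points the right way (steps 3 and 4). Reversal needs special shares, such as few or no LJ culture-driven changes, and the protocol gives no shares. This objection stands, and it limits the claim to 'can'.

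**Time to diagnosis.** A reader might extend the point to this outcome. That fails. Item 7 of the outcomes table runs from randomisation to release of the laboratory result. It does not depend on a change of prescription, and a negative culture can have a release date too.

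**The only measure of speed.** A reader might also infer that the two-month primary outcome misses speed and that this secondary alone can show it. Neither is established. Items 7, 8 and 13 also record times. The 4 to 6 weeks for LJ is incubation only; identification, reporting and the next visit come on top, so some LJ-driven changes may fall near or after month 2.

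**Left to the analysis plan.** No statistical analysis plan was at hand, and censoring rules are commonly placed there. A restricted mean is also a mean time. This stands in part, since such a plan could repair the point. But the protocol itself fixes the measure as a mean and the summaries as mean, standard deviation and median, with no value for non-changers. That is an outcome fixed badly, not only a detail left open.

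**Conclusion.** The point holds in limited form. As written, the first secondary outcome is a comparison between patients selected after randomisation by the primary outcome. At the assumed 40% v 50%, this leaves out 60% of the LJ arm and 50% of the MGIT arm.

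The firm conclusion is that the planned mean ignores any benefit from additional changes and can misstate the size of MGIT's advantage: 5.55 days among changers against a restricted mean gain of 7.2 days in step 4. A wrong direction is possible but not the expected result; step 6 gives 7.0 v 8.6 days against a true gain of 4.5 days. The shares and the day-7 timing are assumptions. The 15-day and 42-day figures are the upper ends of the protocol's laboratory times, used as a stand-in for the day the prescription changes.

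If the outcome's window runs to month 6, the changers averaged are not exactly those of the primary outcome, but the selection problem is the same. The primary analysis is not affected. The change should be made, because this outcome bears on the rationale for the test.

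**What to change.** Redefine the outcome as time from randomisation to first change (starting or stopping TB treatment) in all randomised patients. Use a fixed 60-day horizon, on the same day count as the primary outcome's second month. Censor at loss to follow-up and treat death as a competing event. Report cumulative incidence of change by arm and the difference in restricted mean time to day 60 with its 95% confidence interval. With death competing, this is the difference in area under the cumulative incidence curves. Keep the mean and median among changers as description only, labelled as such.

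The cost is small: a reworded outcome and some more analysis work. One condition must be met first. The sponsor should confirm that the date of starting or stopping treatment is recorded for every patient, because item 9 of the outcomes table names record cards at months 2 and 6 and does not say that exact dates are captured. If they are not, the date has to be added to the study form.

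### Acquired resistance and conversion are measured in groups formed after randomisation, so the unqualified intention-to-treat effect measures are not randomised comparisons for them

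*Protocol*

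**What the plan says.** - **Analysis principle (section 3.11).** "We will used intention-to-treat analysis to calculate the relative risk, the risk difference, the number needed to treat and the 95% confidence intervals". No outcome is exempted, and the same section says "No subgroup analysis will be pre-specified".
- **Acquired resistance (Secondary outcomes).** This is a proportion "in the patients that used the different diagnostic methods and that were classified as treatment failures".
- **Conversion (Secondary outcomes).** Conversion by smear and culture is "due to the anti-TB treatment at the end of the second and sixth month of anti-TB treatment".
- **Treatment failure (Secondary outcomes).** "Proportion of patients that undergo anti-TB treatment failure during the therapy", with no denominator. Section 3.8 defines a failure as a "patient that remains with positive bacteriological test (two samples in a 30 day interval) after 5 months of treatment".
- **Follow-up (section 3.7 and the list of study forms).** All patients are followed for the 8-week diagnostic phase. Only those diagnosed with active TB are followed afterwards, with forms and specimens at week 24.
- **Role of the allocated test (sections 3.8 and 3.9).** A confirmed case "will be defined as the patient with at least one positive culture" for *M. tuberculosis* on either medium. The primary outcome is a change of prescription by month 2, meaning that TB treatment is started or stopped.

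**The concern.** Randomisation makes the arms comparable as whole groups. It does not make the treated patients of one arm comparable with the treated patients of the other when the allocated test helps to decide who is treated. Here the trial's own primary outcome is that the test changes treatment. The better the intervention works on that outcome, the more the two treated groups may differ in composition.

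If one medium finds additional patients whose prognosis differs from the rest, that arm's failure and conversion rates move even though no individual patient does better or worse on treatment. Acquired resistance is two steps removed, since a patient must first be treated and then fail. An NNT from such a contrast has no clear meaning for a hospital choosing a test, because it does not refer to the patients to whom the test is applied.

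Section 2 hypothesises lower morbidity and lethality with the new technology. A reader could therefore easily take a difference in failure, resistance or conversion as an effect of the test, supported by the intention-to-treat label.

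**Working it through.** **Step 1. Who can contribute to each outcome**

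| Outcome | Who can contribute | Fixed at randomisation? |
| --- | --- | --- |
| Primary (prescription change by month 2) | All patients in each group | Yes |
| Conversion, months 2 and 6 of treatment | Treated patients | No |
| Treatment failure | Events only in patients treated for 5 months; denominator open | Only if the denominator is all randomised |
| Acquired resistance | Treatment failures | No |

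Membership of the lower rows depends only partly on the test. Section 3.6 (Randomization) records the physician's opinion on starting treatment before the envelope is opened. Treatment before test results is itself a secondary outcome. Section 3.8 allows culture-negative probable cases.

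**Step 2. The plan's own figure.** Section 3.10 gives at least 770 patients, a 10-point difference, 80% power and a 5% level, but no baseline rate. Assuming 40% v 50%, two-sided, with equal arms:

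n per arm = [0.40×0.60 + 0.50×0.50] × (1.960 + 0.842)² / 0.10² = 0.49 × 7.849 / 0.01 = 384.6, rounded up to 385, so 770 in total.

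The point does not depend on this figure. It only supplies 385 per arm for the illustration.

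**Step 3. Illustration in which the test does not change any treated patient's failure risk.** The LJ sensitivity of 80% to 85% comes from the Rationale. All other inputs are assumptions: TB prevalence 20% to 40%, MGIT sensitivity 85% to 95%, failure risk 10% in TB patients whom LJ would detect and 2% in the others. Let e be the share of culture-missed TB patients who are treated anyway. Treated patients without TB are left out.

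With T TB patients per arm and sensitivities sL and sM:

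- Treated: LJ = T[sL + e(1−sL)]; MGIT = T[sM + e(1−sM)]
- Failures: LJ = T[0.10·sL + 0.02·e(1−sL)]; MGIT = T[0.10·sL + 0.02·{(sM−sL) + e(1−sM)}]

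At 30% prevalence, T = 385 × 0.30 = 115.5. Take sL = 0.80, sM = 0.95 and e = 0:

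- LJ: 92.4 treated, 9.24 failures, 10.0%.
- MGIT: 109.7 treated, 9.24 + 0.02 × 17.325 = 9.59 failures, 8.74%.
- Relative risk among the treated: 8.74/10.0 = 0.87.
- Relative risk per randomised patient: (9.59/385)/(9.24/385) = 1.04.

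Prevalence cancels out of the ratios. Over the sensitivity pairs 80/85, 80/95 and 85/95:

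| Missed patients treated anyway (e) | RR among treated TB patients | RR per randomised patient |
| --- | --- | --- |
| None | 0.87 to 0.95 | 1.01 to 1.04 |
| Half | 0.94 to 0.98 | 1.01 to 1.02 |
| All | 1.00 | 1.00 |

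**Step 4. Sign.** The direction comes from the assumption that the additional cases do better. With the two risks exchanged (2% in LJ-detectable patients, 10% in the others) and e = 0, the LJ arm has 0.02 × 92.4 = 1.848 failures (2.0%). The MGIT arm has 1.848 + 0.10 × 17.325 = 3.58 failures (3.26%). The relative risk is then 1.63 among the treated and 3.58/1.848 = 1.94 per randomised patient. The document does not say which pattern holds.

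**Step 5. Size of the resistance denominator.** With e = 0 and a uniform failure risk of 2% to 10%, failures per arm range from 385 × 0.20 × 0.80 × 0.02 = 1.2 to 385 × 0.40 × 0.95 × 0.10 = 14.6.

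**The case against.** The other side has real substance.

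- **Selection by the test is not total.** A reader might infer that these outcomes are compared only in patients whom the allocated test led to diagnose. The protocol does not support that: patients treated before results and culture-negative probable cases also enter, and smear is done on specimens in both arms. This stands, and it shrinks the likely bias. It does not remove it unless treatment is wholly independent of the allocated culture.
- **The failure line names no denominator.** Read with section 3.11 it could mean failures over all randomised patients, and a statistical analysis plan could settle this. This stands. The problem is explicit for acquired resistance, follows from the definition for conversion, and is conditional for failure.
- **The follow-up medium.** A reader might also infer that conversion is read on a different medium in each arm. Section 3.7 names no medium for follow-up cultures, no passage says that they follow the allocation, and conversion is defined by smear as well as culture. This is a possibility, not a stated rule, and no laboratory change is asked for.
- **The all-randomised denominator is not a clean remedy.** Patients not diagnosed are not followed beyond week 8 and would count as non-failures, so the arm that treats more cases tends to show more failures. This stands: steps 3 and 4 show ratios above 1 with no true effect on treated patients. The contrast is randomised, but it mixes diagnostic yield with treatment outcome and must be described that way.

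**Conclusion.** The point holds in a limited form. For acquired resistance and conversion, and for failure if computed among treated patients, the effect measures promised in section 3.11 would compare groups formed after randomisation and partly by the intervention. They cannot be read as effects of the test under an intention-to-treat label.

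The sign is unknown and the size cannot be derived from the protocol. The relative risks of 0.87 to 1.00 rest on assumed prevalence, MGIT sensitivity and failure risks. The most extreme value in that range requires that culture alone leads to treatment, which the protocol's own provisions contradict. The resistance outcome would in addition rest on roughly 1 to 15 patients per arm under those assumptions.

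Nothing here touches the primary outcome, which is a proportion of each group as randomised. The change should be made, but the trial's main conclusion does not depend on it.

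**What to change.** 1. State the denominator of each secondary outcome.
2. For comparison between arms, report treatment failure and acquired resistance per randomised patient. Say that patients not diagnosed count as non-events, and that the result is a net effect combining diagnostic yield with treatment outcome.
3. Report conversion, and any rate among treated or failed patients, as descriptive by arm, without tests, NNT or causal wording.
4. Limit the intention-to-treat sentence in section 3.11 to outcomes whose denominator is all randomised patients.

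The cost is wording only; no additional data or laboratory work is needed. The downside is smaller proportions (in the first illustration 9.24/385 = 2.4% instead of 10.0%), less precise relative measures for rare events, and no formal comparison of conversion between arms.
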